Study protocol

TITLE

The features behind the beneficial effects of Interval-walking

BACKGROUND

Physical activity is a first line treatment in type 2 diabetes, and the effect of physical activity on glycemic control is well-documented (1;2) but the optimal training approach is yet to be defined.

We have tested Interval-walking (IW) as a novel type of exercise and found that both a long-term training intervention (3) and a single exercise bout (Karstoft et al, JCEM, 2014) is superior to energy-expenditure and time-duration matched continuous walking (CW) exercise. IW, as it has been tested so far, consists of cycles of 3 minutes of fast walking and 3 minutes of slow walking.

The reason why IW is superior to CW upon improving glycemic control is unclear. In that context, at least two factors separate IW from CW: Peak exercise intensity and the alternating intensity pattern. Since some studies have found that continuous training with higher intensity results in greater improvements in metabolic variables compared to continuous training with lower intensity (4-7), the peak exercise intensity in IW may be responsible for the larger improvements in IW compared to CW. Conversely, other studies have found no differences between higher vs. lower continuous intensity training programs on metabolic variables (8-11), and one study has even found that a single lower intensity exercise session improves glycemic control compared with a single exercise session with higher intensity (12). Since most interval-type interventions have shown beneficial changes in metabolic variables (13-16), also when compared to energy-expenditure matched continuous-type interventions (17-20), it may be hypothesized that the alternating rather than the peak intensity is the important part of interval-based training.

With our recent evidence that IW improves glycemic control more than CW, it is of utmost importance to define which characteristics are responsible for the beneficial improvements. Therefore, the objective of this study is to assess the glycemic control in a standardized setting after the following interventions:

- An acute bout of ‘classical’ interval-walking (cycles of 3 min fast and 3 min slow walking; IW-3)
- An acute bout of ‘fast alternating’ interval-walking (cycles of 1 min fast and 1 min slow walking; IW-1)
- No walking (control; CON)

The exercise interventions will be matched with regards walking speed and time-duration.

It is hypothesized that the exercise bouts will improve glycemic control compared with CON but that no differential effect of the exercise bouts on glycemic control will be seen.

EXPERIMENTAL DESIGN

*Sample Size:* Based on our previous study examining glycemic control after acute IW(-3) compared to CON in type 2 diabetic subjects (standardized effect size = 0.95, (21)), power calculations were performed using G*Power (v3.1.9.2, Düsseldorf, Germany). To account for multiplicity, α was set at 0.017 (0.05 / 3), and 1-β was set at 0.80. These analyses indicated that at least 12 subjects should complete the study. If a subject does not complete the study, he or she will be replaced by another subject, but the total number of subjects included will not exceed 24.

*Recruitment, information and informed consent:* Potential subjects are recruited through direct contact, advertising on "www.forsøgsperson.dk" and advertising in local newspapers. Potential subjects contact one of the project participants by telephone and are orally informed about the study. If no exclusion criteria are identified in the phone, an information meeting date is arranged, and the potential subject is informed about the possibility of inviting a private counselor to the information meeting. At least three days prior to the information meeting, written project information including consent form will be sent to the potential subject and he/she will be encouraged to read the information thoroughly.
At the information day, extensive oral information about the scientific study will be given by one of the scientific participants. The information will be given in a closed room where only the scientific participant, the potential subject and the potential private counselor will be present. After the oral information has been given, the potential subject will be asked if he/she wants time to consider before he/she is ready to decide whether or not to participate in the study. If the potential subject does not want time to consider potential participation but is ready to decide and wants to participate in the study, the informed consent form will be signed and the screening will commence. If the potential subject wants additional time to consider whether or not to participate in the study, an agreement about a telephone meeting after approx. one week is made. The subject will be informed of the possibility of contacting one of the scientific participants by telephone, in case of questions. If the potential subject wants to participate in the study, a screening will be arranged and the signed consent form will be brought to the screening by the subject.

*Subjects and screening:* A total of n=12 type 2 diabetes patients will initially be included in the study. A medical examination, medical history, blood chemistry screen, ECG, oral glucose tolerance test (OGTT), Dual x-ray absorptiometry (DXA) scan and a physical fitness test (VO2max test) will be performed. If an individual meets the inclusion criteria, informed oral and written consent will be obtained prior to participation in the study, in accordance with guidelines developed by the ethical committees.

*Inclusion Criteria:*

- Type 2 diabetes mellitus
- Age >30 y
- BMI >18 but <40 kg/m2
- Agreement to pause non-insulin anti-diabetic medication from 2 days before to the end of each intervention

*Exclusion Criteria:*

- Pregnancy
- Smoking
- Contraindication to increased levels of physical activity (22)
- Insulin dependence
- Evidence of thyroid, liver, lung, heart or kidney disease

STUDY DESIGN

Subjects will be instructed to ingest the same food at each day preceding the interventions, to avoid alcohol and caffeine for 24 hours prior to the interventions and to abstain from vigorous physical activity for 48 hours prior to the interventions.

*Interventions:* The 3 interventions will be performed in counter-balanced order and separated by at least one week.

Each intervention day will, besides the differences in interventions, be identical and consist of the following:

- t = -30 min: Arriving fasting (≥8 hours) at lab, acclimatization
- t = 0 min: Blood sample, initiation of intervention (IW-3, IW-1, CON)
- t = 60 min: Blood sample, termination of intervention
- t = 90 min: Initiation of Mixed Meal Tolerance Test (MMTT)
- t = 270 min: Termination of MMTT

METHODS

*Interventions:* At the screening day, a graded walking VO2peak-test (23-25) will be performed using a portable indirect calorimetry system. Based on the peak VO2-rate obtained, two individualized exercise bouts (interventions) will be designed (an interval-walking bout and a continuous-walking bout). Based on the findings from our previous study, the intensities of ‘classical’ and ‘fast alternating’ interval- (fast and slow) walking will be 89 and 54% of the peak VO2-rate, respectively (3). To ensure comparable energy-expenditure, IW-3 and IW-1 bouts will be of 60 min’s duration. All exercise bouts will be performed at a treadmill (Technogym Runrace, Gambettola, Italy), using continuous indirect calorimetric measurements (CPET, Cosmed, Italy) and heart rate monitoring (Polar Electro, Holte, DK). Rate of perceived exertion will be assessed during and after the exercise interventions (26). For the control intervention, subjects will be placed supine for one hour.

*MMTT:* A standardized liquid MMTT (300 kcal with a macronutrient composition that resembles a normal meal; 55% carbohydrates, 30% fat and 15% protein) will be performed after each intervention.

30 minutes after conclusion of the intervention, the MMTT will commence. Blood sampling for subsequent measurements of glucose (NaF plasma tubes), insulin and C-peptide (serum tubes) and incretin and glucagon hormones (EDTA plasma tubes containing aprotinin (500 kiU/mL) and a dipeptidyl peptidase 4 inhibitor (0.01 mmol/L diprotin A) will be performed at the following time points: -30, 0, 30, 60, 90 (start of MMTT), 105, 120, 135, 150, 180, 210, 240 and 270 min. Blood samples for plasma collection will immediately be placed on ice and subsequently centrifuged (2000 g, 15 minutes, 4°C). Samples for serum collection will be left at room temperature for 30 min and centrifuged. Samples will be stored at -80°C until analysis. Plasma glucose will be determined by an enzymatic colorimetric assay (P-Modular, Roche, Switzerland), serum insulin and c-peptide will be measured by electrochemiluminescence immunoassay (E-Modular, Roche, Switzerland) and incretins and glucagon will be measured by radioimmunoassay assays.

RISKS, ADVERSE EFFECTS AND DISCOMFORT

*VO2-max test:* A physical fitness test, where subjects must put in maximum effort. This will cause some degree of breathlessness. VO2max test is a standard method used for scientific purposes in our laboratory.
*DXA scan:* Is not expected to cause significant discomfort. The radiation acquired is so small that it doesn’t cause any risk to subjects. DXA-scan is a standard method used for scientific purposes in our laboratory.

*Pausation of non-insulin anti-diabetic medication:* In order to evaluate the effect of the interventions, it is necessary for subjects to pause medication the days prior to and on the intervention days. It is considered to be without any risk to pause these drugs for shorter time periods.
*Blood sampling:* Will cause minor discomfort in terms of a venous catheter. There is theoretically a risk for infections introduced through the catheter. The blood volume collected is so small that it will cause no symptoms. Blood sampling is a standard method used for scientific purposes in our laboratory.

SUBJECT’S PHYSICAL AND MENTAL INTEGRITY AND PRIVACY

The study will be reported to “Datatilsynet” through Rigshospitalets joint review.

The “Lov om behandling af personoplysninger” will be respected.

ECONOMICAL SUPPORT

[name] has initiated the study. Different private foundations will be applied for economical support (see attached budget). If economical support is obtained, the ethical committee will be notified. Centre for Physical Activity Research (CFAS) will cover the costs not covered by external foundations. No commercial institutions have been or will be applied for economical support. None of the scientific participants have any disclosures to declare.

Subjects will be paid a fee of DKK 2,000 for participation in the study. The fee is taxable. The fee covers discomfort, time consumption and travel expenses. The fee is paid by the end of the subject's participation. If the subject is excluded or choose to withdraw from the trial, a fee equal to the part of the study the subject has completed will be paid.

ETHICAL ASPECTS

The project is, as described above, expected to result in limited risks, adverse effects and discomfort to the subjects. The subjects will benefit from the study in terms of a thorough medical examination and in terms of introduction to effective training methods.
For research in general, the study is sound and important, and it will contribute to our knowledge about how to increase public health in a large and growing cohort of people with lifestyle diseases.

STATISTICAL ANALYSES

All data will be tested for normality and homogeneity of variance using Kolmogorov-Smirnov and Levene tests. Variables that diverge from parametric assumptions will be log-transformed prior to analysis. Variables of interest will be compared via one-way repeated-measure analysis of variance (RM-ANOVA), and where significant interactions arise, Bonferroni post hoc tests will be applied to identify specific differences between means. Relationships between changes in variables will be examined using regression analyses.

BIOLOGICAL MATERIAL

Blood will be collected in the study. This will be used to assess the potential differential changes in variables following the interventions.
Approx. 100 mL blood will be collected per trial day. Total blood sampling will be approx 400 mL. The biological material will, during the study, be stored in a research-biobank. After the study is completed (August 31st, 2016), the biological material will be transferred to a biobank for a maximum of 20 years and after that, it will be destroyed. If any later studies want to make use of the biological material, this will only take place following approval by the ethical committee.
The biological material will not leave Denmark.

EXPECTED OUTCOMES

It is expected that this project will show that the interval-walking exercise bouts are superior to no walking upon improvements in glycemic control in type 2 diabetes patients. This will further improve our understanding of exercise as a concept for fighting lifestyle diseases and potentially lead to changes in the way future exercise interventions are designed and implemented in patient care.

DISSEMINATION

Data will be presented at the American Congress of Sports Medicine (ACSM’s annual meeting) in 2015. At least one manuscript will be produced from the data and published in an international peer-reviewed journal. Positive, negative and inconclusive results will be published.

STUDY LOCATION

Centre for Physical Activity Research (CFAS)
Rigshospitalet
[name]
[name]
Denmark

SCIENTIFIC PARTICIPANTS

[name], responsible investigator, Post doc, Centre for Physical Activity Research (CFAS), Rigshospitalet

[name], cand. scient, Ph.D., associate professor., Department of Biomedical Sciences, Panum, University of Copenhagen,

Research assistent (un-named), Centre for Physical Activity Research (CFAS), Rigshospitalet

[name] [name], DMSc, professor, Centre for Physical Activity Research (CFAS), Rigshospitalet

Reference List

1. Snowling NJ, Hopkins WG (2006) Effects of different modes of exercise training on glucose control and risk factors for complications in type 2 diabetic patients: a meta-analysis. Diabetes Care 29: 2518-2527

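### The plan hypothesises no difference between IW-3 and IW-1 but contains no analysis that can support it, and 12 subjects were sized only for IW-3 versus CON

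*Protocol*

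**What the plan says.** The hypothesis closes the Background section of the Protocol and has two parts. Both exercise bouts are expected to improve glycemic control relative to CON, and between the bouts "no differential effect of the exercise bouts on glycemic control will be seen".

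Under Experimental Design, Sample Size, the calculation is "Based on our previous study examining glycemic control after acute IW(-3) compared to CON in type 2 diabetic subjects", with "standardized effect size = 0.95". Alpha is 0.05 divided by 3, given as 0.017, and "1-β was set at 0.80". The result is that "These analyses indicated that at least 12 subjects should complete the study". Non-completers are replaced, and "the total number of subjects included will not exceed 24". No effect, margin or power is given for IW-3 versus IW-1.

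Under Statistical Analyses, variables are compared by one-way repeated-measures ANOVA. After a significant result, "Bonferroni post hoc tests will be applied to identify specific differences between means". The protocol gives no equivalence margin, no confidence-interval criterion and no rule for when the second part of the hypothesis counts as supported.

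**The concern.** The second part of the hypothesis is a claim of no difference, and the planned tests can only show a difference. As the plan stands, the one outcome that could seem to favour that claim is a non-significant IW-3 versus IW-1 comparison. In a small trial, that outcome is common whether or not the bouts differ. Dividing alpha by three is conservative for claiming a difference, but it makes this predicted null result easier to obtain.

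The Background sets out to identify which features of interval-walking produce its benefit. IW-3 versus IW-1 is the only comparison between two alternation patterns, so it bears directly on that aim. At stake is a conclusion that alternation frequency does not matter, drawn from data that could not exclude a sizeable difference.

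**Working it through.** **Inputs from the Protocol (Sample Size).** Standardized effect 0.95 for IW-3 versus CON, α = 0.017, power 0.80, n = 12 completers, each receiving all three interventions.

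**Assumptions, because the Protocol does not state them.** (a) 0.95 is a paired effect size, that is, mean difference divided by the SD of within-subject differences. (b) The SD of IW-3 minus IW-1 equals that of IW-3 minus CON; this is varied in step 4. (c) Tests are two-sided unless noted. Differences, margins and half-widths are in units of the SD of paired differences.

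**1. The stated sample size.** The normal approximation n = ((z₁₋α/₂ + z₀.₈₀)/d)² gives ((2.387 + 0.842)/0.95)² = 11.55, so 12. The stated figure is reproduced. The noncentral t distribution gives power 0.795 at n = 12 one-sided, and 0.68 two-sided (15 needed for 80%). The 12 therefore rests on a normal approximation or, nearly, on a one-sided test. In either case it concerns IW-3 versus CON.

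**2. Precision for IW-3 minus IW-1 at n = 12.** The half-width is t(11)/√12:
- 90%: 1.796/3.464 = 0.52
- 95%: 2.201/3.464 = 0.64
- 98.3%: 2.809/3.464 = 0.81

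**3. Chance of a non-significant result when the bouts truly differ.** Two-sided paired t test, noncentrality d√12:

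| True difference | α = 0.017 | α = 0.05 |
|---|---|---|
| 0.475 (half of 0.95) | 83% | 68% |
| 0.80 | 49% | 29% |
| 0.95 | 32% | 15% |

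The difference detectable with 80% power is 1.07 at α = 0.017 and 0.89 at 0.05. Simulating the ANOVA step before the Bonferroni test barely changes this: at a difference of 0.5, power is 19% with or without it. Even with 24 completers, the detectable difference at 0.017 would be 0.70.

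**4. Varying assumption (b).** If the SD of IW-3 minus IW-1 is r times that of IW-3 minus CON, half the raw planning effect becomes 0.475/r. The last column is the power of two one-sided tests (5% each) when the bouts are identical and the margin is half the raw effect.

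| r | 0.475/r | Non-significant, α = 0.017 | Non-significant, α = 0.05 | Equivalence power |
|---|---|---|---|---|
| 1.0 | 0.475 | 83% | 68% | 8% |
| 0.8 | 0.594 | 72% | 53% | 26% |
| 0.7 | 0.679 | 63% | 43% | 43% |
| 0.5 | 0.950 | 32% | 15% | 85% |

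**5. What 12 subjects could show formally.** By simulation with r = 1 and identical bouts, equivalence power is 8% for a margin of 0.475, 66% for 0.80 and 85% for 0.95. For 80% power, about 40 subjects are needed at a margin of 0.475, about 15 at 0.80 and 12 at 0.95. The Protocol gives no margin; these values only show the range.

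**The case against.** The strongest reply is that the Protocol never says a non-significant result will be taken as equivalence. The hypothesis is an expectation, Expected Outcomes speaks only of superiority to no walking, and Dissemination promises publication even if results are inconclusive. This stands. A reader might infer that the trial is set to report that alternation frequency does not matter, but that is a prediction about reporting that the document does not support. What remains is that the hypothesis is explicit and nothing planned can support it.

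A margin, an interval level and an interpretation rule could sit in a statistical analysis plan that is not shown. That is fair as to detail. The hypothesis and the sample size are fixed in this Protocol, however, and with r = 1 a later margin would reach 80% power at n = 12 only if it were about 0.95.

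The size of the problem depends on an unknown SD. The bouts are matched on speed and duration, so their difference may vary less than exercise minus rest. This also stands, which is why step 4 of the working gives a range. At r = 0.5 the problem is much smaller.

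Two further readings go too far. One is that the design simply misses large differences: at α = 0.017 it detects 0.80 about half the time and 0.95 about two times in three, so it often misses moderate to large ones. The other is that IW-3 versus IW-1 is the only new contrast: the Background says interval-walking has so far been tested with 3-minute cycles, so IW-1 versus CON is new too, and the planned tests suit it.

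Finally, correcting all three pairwise comparisons is conventional and protects against falsely claiming that the bouts differ. Taking one contrast out of the 0.05/3 division would reopen the sample size calculation and is not needed here.

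**Conclusion.** The point holds in this form: the plan states a no-difference hypothesis for IW-3 versus IW-1, provides only tests of difference, and sizes the trial for another contrast. It therefore cannot support one part of its own hypothesis. With 12 completers, a true difference of half the planning effect would go undetected 83% of the time at α = 0.017 under equal SDs, and roughly 63% to 72% of the time at SD ratios of 0.7 to 0.8. These figures assume that 0.95 is a paired effect size and that tests are two-sided.

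The comparisons with CON are not affected by this point. Nor does it show that the investigators intend to read non-significance as equality; the fault is that the plan does not rule it out and offers nothing else.

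**What to change.** Reword the hypothesis and add a conclusion rule:

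- Report IW-3 minus IW-1 as an estimate with a confidence interval: 90% if two one-sided tests are used, otherwise 95%.
- State that a non-significant difference will not be read as no differential effect.
- Allow that conclusion only if the interval lies wholly inside a margin fixed and justified before the data are seen.
- If no defensible margin is attainable with 12 completers, label the contrast estimation only.

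The 0.05/3 division can stay for the tests of difference.

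The cost is protocol wording and a more modest conclusion on IW-3 versus IW-1. The estimation-only route needs no extra subjects. Powering a formal equivalence claim at a margin tighter than about 0.95 SD would need more than 12, and at 0.475 (about 40) more than the cap of 24.

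### Replacements are not tied to the vacated treatment order, and the one-way RM-ANOVA has no period term and leaves non-completers' finished visits unused

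*Protocol*

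**What the plan says.** Three parts of the protocol bear on this point.

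- **Experimental Design, Sample Size.** The target is counted in completers: "These analyses indicated that at least 12 subjects should complete the study". For the rest: "If a subject does not complete the study, he or she will be replaced by another subject", with the limit that "the total number of subjects included will not exceed 24". The subjects and screening paragraph starts with 12 included, so there is no allowance for dropout.
- **Study Design, Interventions.** "The 3 interventions will be performed in counter-balanced order", with at least a week between visits. The number of orders is not given, and neither is the order that a replacement receives.
- **Statistical Analyses.** "Variables of interest will be compared via one-way repeated-measure analysis of variance (RM-ANOVA"), followed by Bonferroni comparisons. Intervention is the only factor that a one-way model contains. No period or sequence term is named, and nothing is said about partial data.

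**The concern.** Each rule is ordinary alone; the difficulty comes from combining them. A target counted in completers, together with a model that in its standard form needs a value under all three conditions, means that someone who finishes one or two visits and then leaves contributes nothing to the comparison.

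Counter-balancing keeps a visit effect out of the intervention contrasts when the model ignores visit. That protection holds only while the orders among the analysed subjects stay balanced. If a replacement gets a different order from the person who left, part of any visit effect enters the contrasts, and the stated model cannot take it out. Even with perfect balance, leaving period out puts visit variation into the error term, which matters with 12 subjects.

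Replacement also restores the number of completers without restoring the group enrolled. If failure to complete is related to the exercise bouts, the result describes those able to complete them.

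**Working it through.** **The plan's own figure.** Inputs from the Sample Size paragraph: "standardized effect size = 0.95" and "α was set at 0.017 (0.05 / 3), and 1-β was set at 0.80". The test and its sidedness are not stated; I treat 0.95 as the mean paired difference divided by the standard deviation of the differences.

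- Normal approximation, two-sided: n = ((2.387 + 0.842)/0.95)² = 11.55, rounded up to 12. This is the stated figure.
- Exact paired t-test: 13 if one-sided (power 0.795 at n = 12), 15 if two-sided (power 0.68 at n = 12).

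The point below does not depend on which was used. It takes 12 completers as the target.

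**How often the replacement rule would act.** The protocol gives no dropout rate, so a range is assumed. The chance that at least one of the first 12 needs replacing is 1 − (1 − rate)¹². The number included to obtain 12 completers is 12/(1 − rate), rounded up.

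| Assumed dropout | At least one replacement | Included | Left out |
|---|---|---|---|
| 5% | 46% | 13 | 1/13 = 8% |
| 10% | 72% | 14 | 2/14 = 14% |
| 20% | 93% | 15 | 3/15 = 20% |
| 30% | 99% | 18 | 6/18 = 33% |

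Rounding up puts some shares above the dropout rate itself. The ceiling with 12 completers is (24 − 12)/24 = 50%.

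**Chance of losing exact balance.** Assume six orders with two subjects each and a random order for each replacement. One replacement restores balance with probability 1/6, about 17% (16% by simulation); two do so with probability about 5%. If each replacement takes the vacated order, balance is always kept.

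**Size of the shift.** Let the outcome drift by d per visit. For a pair of interventions, a subject's contrast picks up d times the difference in visit number. Over the six orders these differences are −2, −1, −1, 1, 1, 2, which sum to zero, so a balanced set has no shift. Replacing a subject with difference x by one with difference y moves the mean contrast by (y − x)d/12.

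- Largest: x = 2, y = −2 (control first and the bout last becomes the reverse), giving 4d/12 = 0.33d.
- Average absolute shift over random original and replacement orders: the 36 ordered pairs have |y − x| summing to 56, so 56/36 = 1.56, and 1.56d/12 = 0.13d. This average includes the 1 in 6 chance of a match. Among the 30 mismatched pairs it is (56/30)d/12 = 0.16d.
- If a three-order Latin square is used instead, the differences are −1, −1, 2 (or the same with signs reversed), and the largest shift is 3d/12 = 0.25d.

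**Cost of a period term.** With 12 subjects and three conditions the one-way RM-ANOVA has (12 − 1)(3 − 1) = 22 error degrees of freedom. Period uses two, leaving 20.

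**The case against.** The strongest reply is that analysis sets, partial data and covariates are usually settled in an SAP, which is not shown, and that the protocol never says completed visits are discarded. That is fair as far as it goes: the loss follows from standard RM-ANOVA and the completer-based target, not from an explicit exclusion. But the model is named in the protocol, and replacement and order allocation operate during enrolment, so an SAP cannot undo them.

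Several stronger readings are tempting, and the document does not support them.

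- **Half of those enrolled will be lost.** 50% is the ceiling set by the cap with 12 completers, not a forecast. Three single-day visits may produce few dropouts, and the included count may cover screening failures, who have no visit data to lose.
- **Each dropout after two visits costs one of 12 planned pairs, or 8%.** Replacement restores the 12 pairs. What goes unused is an additional pair in one of the three contrasts.
- **The least fit are the ones replaced.** The Methods section sets intensity relative to each subject's own peak VO2, and no tolerance data are given.
- **The balance will break.** Replacing a subject is compatible with filling the vacated slot. The text leaves this open. The six orders are also an assumption.

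It is also true that d may be small: visits are at least a week apart, with the same procedures and the same diet and activity instructions. And a mixed model does not supply outcomes for people who cannot finish a bout. For an acute mechanistic crossover, completers are a defensible population if that limit is stated.

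**Conclusion.** The point holds in a moderate form. As written, the protocol does not protect its own counter-balancing when a subject is replaced, and it commits to a model that cannot adjust for visit and makes no use of non-completers' finished visits. Under six orders and linear drift, one mismatched replacement moves a pairwise contrast by no more than 0.33d; a randomly ordered one moves it by 0.13d on average in absolute size. Whether that matters depends on d, which the document does not give. The share of included subjects left out is about 8% to 20% at assumed dropout of 5% to 20%.

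A reader might infer that the trial's result is biased or that its population is already distorted. The documents show neither: they leave both possible. The case for changing the plan is that the better method is available at almost no cost.

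**What to change.** Keep the replacement rule and the cap of 24, and make three changes.

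1. State that each replacement takes the order of the subject replaced.
2. Make the main analysis a linear mixed model with fixed effects for intervention and period and a random subject effect, using every completed visit. Keep the completers-only RM-ANOVA as a sensitivity analysis.
3. Report the number who did not complete, by intervention.

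This needs no extra subjects or visits. The costs are two error degrees of freedom for period (22 to 20 with 12 complete subjects) and a main table in which some subjects have fewer than three visits. Subjects with two visits add a pair to one contrast; those with one visit add almost nothing to within-subject comparisons.

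The mixed model assumes that missing visits are ignorable. It does not remove selection by exercise tolerance, so the conclusions should be limited to patients able to complete the bouts.

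### Levene's test is the wrong check for this within-subject RM-ANOVA, which needs sphericity; the overall F may be mildly liberal, and pairwise results suffer only if post hoc tests use the pooled residual

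*Protocol*

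**What the plan says.** The trial is a three-condition crossover. Under Study Design, Interventions: "The 3 interventions will be performed in counter-balanced order and separated by at least one week".

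The Statistical Analyses section fixes four things:

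- The assumption checks: "All data will be tested for normality and homogeneity of variance using Kolmogorov-Smirnov and Levene tests".
- The remedy if they fail: "Variables that diverge from parametric assumptions will be log-transformed prior to analysis".
- The model: "Variables of interest will be compared via one-way repeated-measure analysis of variance (RM-ANOVA".
- The follow-up: "Bonferroni post hoc tests will be applied to identify specific differences between means". The error term of these tests is not given.

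Sphericity and epsilon corrections are not mentioned. The sample size paragraph sets the level for each comparison: "To account for multiplicity, α was set at 0.017 (0.05 / 3), and 1-β was set at 0.80". The hypothesis closing the Background is that "the exercise bouts will improve glycemic control compared with CON but that no differential effect of the exercise bouts" will be seen.

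**The concern.** There is one group of subjects, so the only groups Levene's test could compare are the three conditions, and those are correlated measurements on the same people. The test looks at the marginal variances. One-way RM-ANOVA needs equal variances of IW-3 minus IW-1, IW-3 minus CON and IW-1 minus CON, and these also depend on the correlations. Equal marginal variances neither guarantee sphericity nor are required for it.

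The design gives a reason to doubt sphericity. The two bouts share duration and target intensities, whereas CON is an hour of lying still. How a given subject responds to exercise should largely cancel in IW-3 minus IW-1 but remain in each exercise-minus-CON difference.

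Two things are at stake. An uncorrected overall F is liberal when sphericity fails. If the post hoc tests also use the pooled residual, that residual averages a small difference variance with two larger ones. It is then too small for exercise versus CON and too large for IW-3 versus IW-1.

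**Working it through.** **Inputs from the protocol.** 12 completers; three conditions; 0.05/3 per comparison; standardised effect 0.95 for IW-3 versus CON, read here as the mean difference divided by the SD of the differences.

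**Assumed, because the protocol gives neither.** Equal SDs (set to 1), correlation r_b between the bouts, and correlation r_c of each bout with CON, both shown over a range.

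**The plan's own figure.** The two-sided normal approximation gives ((2.387 + 0.842)/0.95)² = 11.6, so 12. By noncentral t, a two-sided paired test on 12 subjects has power 0.68. One-sided, it is 0.795. The point below does not contest the 12, but the 0.68 recurs as the power of a pair-specific test.

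**Step 1: difference variances.** Var(difference) = 2(1 − r). The pooled residual implies the mean of the three. For r_b = 0.9 and r_c = 0.6:

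- IW-3 minus IW-1: 2 × 0.1 = 0.2
- each bout minus CON: 2 × 0.4 = 0.8
- pooled: (0.2 + 0.8 + 0.8)/3 = 0.6
- ratios to pooled: 0.33 and 1.33

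**Step 2: epsilon.** The two orthonormal contrasts have variances λ₁ = 1 − r_b and λ₂ = 1 + (r_b − 4r_c)/3, and ε = (λ₁ + λ₂)²/[2(λ₁² + λ₂²)]. For 0.9 and 0.6, λ₁ = 0.1 and λ₂ = 0.5, so ε = 0.36/0.52 = 0.69.

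**Step 3: error rates by simulation.** n = 12, normal data, at least 40,000 trials per setting. Repeat runs agree to within about 0.2 percentage points. The pairwise columns use the pooled residual on 22 df. Power is for a true IW-3 versus IW-1 difference of 0.95 SD of its own differences.

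| r_b / r_c | ε | Overall F error (5%) | Exercise vs CON error (1.7%) | IW-3 vs IW-1 error (1.7%) | IW-3 vs IW-1 power |
|---|---|---|---|---|---|
| 0.7 / 0.7 | 1.00 | 5.1% | 1.7% | 1.6% | 75% |
| 0.8 / 0.7 | 0.94 | 5.3% | 2.4% | 0.6% | 62% |
| 0.8 / 0.6 | 0.86 | 5.9% | 3.0% | 0.3% | 50% |
| 0.9 / 0.6 | 0.69 | 6.8% | 3.9% | 0.04% | 19% |
| 0.95 / 0.6 | 0.60 | 7.8% | 4.7% | about 0% | 3% |
| 0.6 / 0.8 (reversed) | 0.80 | 5.9% | 0.7% | 4.6% | 87% |

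Requiring a significant overall F first changes the pooled pairwise error rates by less than 0.1 percentage point.

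**Step 4: the same data with the alternative methods.** The Greenhouse-Geisser F has an error of about 4.1% to 5.1% across these settings. Paired t-tests on each pair's own differences (11 df) keep an error of 1.6% to 1.8%, with power 68% for every pair at 0.95.

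**Step 5: would Levene's test warn?** At 0.9 and 0.6 it rejects in about 2% of trials when centred on means and about 1% when centred on medians. On spherical data with all correlations 0.7 it rejects in about 1% and 0.5%. Both are below the nominal 5%, and the test hardly separates the two cases.

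**The case against.** A reader might infer that the plan as written is biased towards its own hypothesis: exercise too easily beats CON, and the bouts are too seldom found to differ. The protocol does not support that, for three reasons.

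- **The error term is not stated.** Bonferroni post hoc tests can be run on the pooled residual or as separate paired tests. With separate paired tests the pairwise error rates are not distorted, and only the overall F is affected.
- **The correlations are assumed, and the steeper rows are strong cases.** At 0.9 and 0.6, if visit-to-visit noise accounts for the 0.2 in the bout difference, the remaining 0.8 − 0.2 = 0.6 must be true variation in response to exercise. That is an SD of √0.6 = 0.77, against a mean effect of 0.95 × √0.8 = 0.85. At 0.8 and 0.7 the distortions are small.
- **The direction is not fixed.** If the bouts correlated less with each other than with CON, the bias would reverse, as the last row of the table shows.

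It can also be said that an epsilon correction and the post hoc error term are details a SAP often settles. That is fair, and their absence alone would be no finding.

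All of this stands, and it limits the size and direction of the harm. It does not rescue the check. The protocol names an independent-groups test and a single remedy for a within-subject analysis, and a SAP that followed the text would carry both forward.

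**Conclusion.** The point holds in a limited form. Levene's test with a log-transform is the wrong check and the wrong remedy for this RM-ANOVA, and a failure of sphericity would pass unnoticed. For correlations from 0.8 and 0.7 to 0.95 and 0.6, with equal SDs and 12 completers, the cost to the overall F is an error of about 5.3% to 7.8% instead of 5%.

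A pairwise distortion that favours the hypothesis needs two further conditions: post hoc tests on the pooled residual, and a higher correlation between the bouts than with CON. The second is plausible from the matching of the bouts but is not shown. The first is left open. If both hold, the hypothesis that the bouts do not differ is the more exposed part, because a true difference of 0.95 SD would be found with power of 62% down to 3% instead of 68%.

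The wording should be corrected before analysis. Confidence in the size is moderate, because every correlation is an assumption.

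**What to change.** In Statistical Analyses:

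1. Delete the Levene check.
2. Apply the Greenhouse-Geisser correction to the overall RM-ANOVA F, without making it depend on a preliminary test.
3. State that each pairwise comparison is tested on its own within-subject differences: Bonferroni-adjusted paired t-tests with n − 1 degrees of freedom.

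A mixed model with unstructured covariance is an alternative, not a requirement.

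This changes analysis wording only; no visit, sample or measurement is affected. The cost is degrees of freedom: 11 instead of 22 per comparison at n = 12. Under sphericity, power for exercise versus CON at an effect of 0.95 is about 68% instead of the 75% that pooled-error tests would give. Where the bouts correlate more with each other than with CON, the pooled tests show higher power still (81% to 84% at 0.8/0.6 and 0.9/0.6), but that comes with an inflated error rate.
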